### Sample/participants

Participants: The patients will be recruited from the Oncology Hospitalisation Unit at the CAUSA when they will be hospitalised. The Unit’s investigators will invite patients to participate in the study by explaining the details of the clinical trial, and they can then be included once they have given their verbal and written consent, and meet the following selection criteria: (A) Inclusion criteria: Participants must have a pathological diagnosis of an oncological disease, be over 18 years of age, be hospitalised at the time of recruitment in the Oncology Hospitalisation Unit at the CAUSA, having a score of 15–55 points on the Barthel Index (BI), having a score of 4 or more on the visual-analogue scale (VAS) for cancer-related asthenia and have signed an informed consent form indicating voluntary agreement to participate in the study. (B) Exclusion criteria: not having an adequate cognitive state to be able to comprehend and follow the orders provided (fewer than 23 points on the Mini Mental State Examination, MMSE), and having a haemoglobin level lower than 10 g/dL. (C) Withdrawal criteria: disease progression which brings the patient to a terminal situation or to death, and non-completion of the follow-up and final assessments.

Assignment, randomisation and blinding: After recruitment, individuals will be assigned by a randomisation process to one of two study groups: Experimental Group or Control Group. Detailed in Fig. 1.

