**Fig. 1 Fig1:**
[figure not shown]
Study design. The enrolled participants will be randomly assigned to one of the study groups and will be assessed at three pre-specified time p

We will employ a simple randomisation process that consists of generating a table of random numbers of the same size as the estimated study sample with Microsoft Excel 2020 to assign subjects to each of the study groups. For even numbers, the subject will be assigned to the Experimental Group, and for odd numbers, the subject will be assigned to the Control Group. Randomisation, recruitment and assignment of subjects to each group will be performed by research staff not involved in the evaluations or interventions in each group, which will avoid potential bias in the study.

The participating subjects will not be blinded, due to the specific characteristics of the intervention in each group. However, the researchers responsible for the study measurements and statistical analysis will be blinded, with the intention of avoiding any contamination between groups, thus increasing the rigour of the study process.

Sample size: The sample size has been estimated based on the potential modification of one of the main outcome of the study—the score on the Barthel Index. For this calculation, we have considered the results obtained in a similar, where a modification of 17 points in the BI score was obtained, as a difference attributable to the intervention, considering this as the difference between the modification of the experimental group and the control group [20]. With these premises, accepting an alpha risk of 0.05 and a beta risk of 0.2 in a bilateral contrast, with 50 individuals (25 subjects in the experimental group and 25 in the control group, the statistical power was 90 % to recognize as statistically significant a change of 17 points between both groups in the BI score. The sample size was estimated using the programme EPIDAT 4.2.

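### The sample-size statement gives a beta of 0.2 and a power of 90% for the same 25 + 25 patients without reconciling them, and the 90% holds at best with no loss of outcome data

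*Protocol article*

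**What the plan says.** The calculation is in the sample-size paragraph under Sample/participants in the protocol article. It rests on the Barthel Index, which the section on the variables names as the main variable.

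- **Effect:** taken from one similar study, "where a modification of 17 points in the BI score was obtained, as a difference attributable to the intervention". The paragraph defines it as a between-group difference in change: "considering this as the difference between the modification of the experimental group and the control group".
- **Error rates:** "accepting an alpha risk of 0.05 and a beta risk of 0.2 in a bilateral contrast".
- **Sample size:** "with 50 individuals (25 subjects in the experimental group and 25 in the control group".
- **Result:** "the statistical power was 90 % to recognize as statistically significant a change of 17 points between both groups".
- **Tool:** "The sample size was estimated using the programme EPIDAT 4.2".

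The paragraph gives no SD, no standardised effect and no allowance for loss. In the same section, the withdrawal criteria cover progression to a terminal state, death and "non-completion of the follow-up and final assessments". The data analysis section says that the analysis will be by intention to treat.

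**The concern.** A beta of 0.2 is a power of 80%, and a power of 90% is a beta of 0.1. Both figures stand in one sentence, for the same number of patients and the same 17-point difference, and nothing says how they relate. The reader cannot tell which is the design target and which, if either, is the result of the calculation.

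The 90% is also tied to 25 + 25 patients as if all of them would give Barthel scores. The patients are hospitalised for cancer and have a Barthel Index of 15 to 55 at entry, and the protocol itself makes rules for withdrawing those who decline, die or miss assessments.

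This paragraph is the article's only justification for the sample size. If the trial finds no difference, readers will judge that result against the stated power, so the figure should be one that can be checked and that refers to the patients who will be analysed.

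**Working it through.** **Inputs from the article:** two-sided alpha 0.05; difference in Barthel change Δ = 17; n = 25 per arm; stated beta 0.2; stated power 90%.

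**Input not in the article:** the SD of Barthel change, σ. The stated power therefore cannot be reproduced. What can be done is to solve for the σ that each stated power implies.

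**Formula.** For a two-sample t-test with n per arm, the noncentrality is λ = Δ / (σ·√(2/n)), on 2n − 2 degrees of freedom. Power is the probability that a noncentral t variable with this λ lies beyond the two-sided critical value, which is 2.011 on 48 degrees of freedom.

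**Step 1: implied SDs at 25 per arm.**

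- Power 90%: σ = 18.17. Check: λ = 17 / (18.17 × √(2/25)) = 17 / (18.17 × 0.2828) = 3.31, power 0.900.
- Power 80%: σ = 21.02. Check: λ = 17 / (21.02 × 0.2828) = 2.86, power 0.800.

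The normal approximation σ = Δ·√(n/2) / (z₀.₉₇₅ + z_power) gives nearly the same:

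- 90%: 17 × 3.536 / (1.960 + 1.282) = 18.5
- 80%: 17 × 3.536 / (1.960 + 0.842) = 21.5

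No single SD gives both powers at this sample size.

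**Step 2: how much the answer depends on the missing SD.** At 25 per arm, by the t-test and with assumed SDs, power is about 98% at SD 15, 84% at SD 20 and 65% at SD 25. So 90% is attainable, but only if the SD is about 18 or less.

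**Step 3: loss of outcome data.** The article gives no loss rate, so the rates below are assumptions. They are applied as n = 25 × (1 − loss).

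| Assumed loss | Evaluable per arm | Power if σ = 18.17 | Power if σ = 21.02 |
|---|---|---|---|
| 0% | 25 | 90% | 80% |
| 10% | 22.5 | 87% | 76% |
| 20% | 20 | 82% | 70% |
| 30% | 17.5 | 77% | 64% |

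**Step 4: can the two figures be reconciled?** At σ = 18.17, 19 evaluable per arm gives 80.1% and 18 gives 77.8%. So 80% power needs 19 per arm, or 38 in all, and 50 randomised would tolerate a loss of 1 − 38/50 = 24%. Beta 0.2 as the target and 90% as the power with no loss would then fit together, but the article does not say this.

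**Step 5: allocation.** The article uses simple randomisation, so an exact 25/25 split is not assured. At σ = 18.17, a 20/30 split gives about 89%. This is too small to matter.

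**The case against.** The strongest reply is that the sentence can be read without contradiction. The authors accept a beta of at most 0.2, then report that the chosen 50 patients give 90%. One SD of about 18 serves both figures, and 50 would absorb roughly 24% loss before power fell below 80%. This reading is possible, and for that reason the sentence is better called unreconciled than a proven arithmetic error. It does not rescue the text, which nowhere describes 0.2 as a ceiling or 50 as including a margin, and which reports the 90% without qualification.

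A second reply is that an article condenses the full protocol, where the SD may well be given. That is fair: the absent SD taken alone is missing detail, not an error. It matters here because nothing else in the article can settle which of the two powers is meant.

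A third reply is that the withdrawal criteria forecast no rate, and that the analysis is by intention to treat. The first half is right, so every loss rate used here is an assumption. The second half does not help, because analysing patients as randomised does not by itself supply Barthel scores that were never collected.

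A reader might go further and infer that the design does not deliver 90%, or that its true power is nearer 65 to 80%. The document does not support either statement. Without the SD, power below 90% cannot be shown, and an SD under about 18 would give more than 90% with all 50 evaluable. The lower end of that range needs both the larger implied SD and an assumed 30% loss.

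**Conclusion.** The point stands as one of inconsistent reporting. The article attaches a beta of 0.2 and a power of 90% to the same 25 + 25 patients and 17-point difference and does not say how they relate. They imply SDs of change of about 21.0 and 18.2, and only one power can hold at a given SD. The 90% cannot be reproduced from the article.

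Whichever figure is right at 25 per arm, it is a best case that needs outcome data from all 50. Over assumed losses of 10% to 30%, 90% becomes about 87% to 77%, and 80% becomes about 76% to 64%. These results assume a two-sample t-test on change with equal SDs, equal arms, and power determined by the patients with data. They show how sensitive the stated figure is and are not an estimate of the trial's true power.

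**What to change.** Keep n = 50 and restate the sample-size sentence with:

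1. One power figure.
2. The SD of Barthel change actually entered in EPIDAT, with its source. The 18.2 above must not be inserted: it was solved from the 90%, so using it would make the 90% true by construction.
3. The expected loss, and the power for the number then expected to be evaluable.

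If beta 0.2 was the planning target and 50 includes a margin for loss, the sentence should say so and drop the unqualified 90%. At the SD that the 90% implies, the margin is from 50 down to about 38 evaluable patients, or about 24%. The sponsor should recalculate this from the real SD.

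The cost is a rewording with no extra patients. The stated power will look less favourable than an unqualified 90%.

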### Procedures and data collection

#### Evaluations and study plan

Participants will be assessed at three points during the study: Firstly, the baseline assessment at the beginning, the second assessment after seven days, and a third final assessment, before the patients are discharged from hospital. The baseline assessment will be performed after recruitment and before randomisation and assignment of subjects to the corresponding group. This initial assessment includes the recording of the independent variables and the primary and secondary outcome variables of the study. Then, after randomisation, the corresponding intervention will begin to be applied to each group. Subsequently, the other further assessments will be carried out, one after seven days, considered as the follow-up assessment, and another at hospital discharge, considered as the final assessment. This can be seen in more detail in Table 1.

**Table 1 Tab1:** Timeline and dimensions assessed at the time points

	STUDY PERIOD							
	**Enrolment**	**Allocation**	**Post-allocation**					**Close-out**
**TIMEPOINT**	***Month 1-2***	***Month 2-3***	***M4***	***M5***	***M6***	***M7***	***M8***	***M9-M12***

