**INTERVENTIONS**:								
***[Experimental Intervention]***								
***[Control Intervention]***								
**ASSESSMENTS**:								
***[BASELINE ASSESSMENT]***		X						
***[FOLLOW-UP ASSESSMENT]***								X
***[FINAL ASSESSMENT]***								X
***DISSEMINATION OF RESULTS***:								X

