#### Interventions

Conventional standard of care will be applied in both groups, explaining to each subject participating in the study the importance of compliance and adherence to the prescribed pharmacological treatment and the established guidelines personalised to their specific health needs. In the days prior to hospital discharge, they will also receive, as a part of the intervention, a health education programme with an informative talk and written guidelines, mainly focused at reinforcing and promoting an active and healthy lifestyle.

The difference of the intervention in the experimental group will be due to the fact that we will also implement the intervention with a multimodal programme of physical exercise and functional rehabilitation lasting one month. This will consist of:

1. A prescription for multimodal physical exercise. In the Oncology Hospitalisation Unit at the CAUSA, as in other studies already initiated [19], we will carry out the following design of a multimodal physical exercise programme. A supervised and structured program will be implemented in these patients for one month. This will consist of two short 15–20-minute sessions performed daily, one in the morning and one in the afternoon. The sessions will be structured according to the recommendations of the American College of Sports Medicine (ACSM) [29, 30], with an initial warm-up (2–3 min), the main section comprising the principal physical exercises (8–12 min), and a final cool-down and relaxation phase (5 min).

Parts of a standard session: The warm-up will consist of exercises designed to promote joint mobility and muscle activation. The main section will combine aerobic and balance exercises with low-load strength exercises targeting upper and lower quadrant muscle groups. The dosage and load will always be adapted according to patient evaluations performed beforehand and will follow a progression in difficulty with the aim of achieving an intensity at 50–75 % of each patient’s maximum heart rate or a perception of moderate effort on the Borg Scale. After 15 days of the program, the second evaluation will be carried out and the program may then be modified by adapting the load. Finally, the cool down will consist of gentle muscle stretching and relaxation exercises.

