#### Work plan and visit structure

Once the possible study candidates have been identified in the Oncology Hospitalisation Unit at the CAUSA, an interview with each individual will be organised to explain the purpose of the study to them and thereafter, invite them to sign the informed consent to their participation. Each participant will complete 3 planned evaluation visits. One at baseline, prior to randomisation, and two follow-up visits 15 days and 1 month after the first visit. The structure of all three 3 visits will be the same and each will last approximately one hour. In addition, there will be a telephone follow-up 3 and 6 months after the randomisation. The study variables will be evaluated during these visits, as specified in Table 1.

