#### Follow-up visits at 15 days and 1 month

These visits will be identical to the baseline evaluation, except that the sociodemographic variables will only be collected at the baseline evaluation. The follow-up visits will be completed in the Clinical Teaching Assistance Unit in the Faculty of Psychology at the University of Salamanca, Spain.

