## Discussion

Cancer-related asthenia is considered the most common symptom associated with tumours and their treatment and is an essential factor in the functional deterioration of individuals with cancer [5]. There is growing interest in conducting clinical trials on the influence of physical exercise on the quality of life of cancer patients, although how these beneficial influences might affect the autonomy of patients in their daily lives remains to be addressed. However, these beneficial effects have been observed in daily clinical practice in patients with cancer-related asthenia in terms of physical improvements. Nonetheless, difficulties in generalising this physical improvement to occupational performance have also been noted [7–9].

As oncological clinicians, one of the biggest problems we face on a daily basis is that, although the acute patient symptoms will have been optimally resolved at the time of hospital discharge, there is still room for improvement in functional terms. With the planned follow-up described in this article, we intend to resolve this handicap by incorporating a prescription for specific rehabilitation methods for patients. We consider it essential to include ADL re-education techniques as part of the multimodal physical exercise rehabilitation methods [9].

Furthermore, in order to favour both an adequate intervention environment as well as self-management of situations by patients, our study proposes a supervised home-based intervention adapted to the specific situation of each patient with moderate cancer-related asthenia for implementation after their discharge from hospital. This meets the NCCN recommendations that better, more accessible physical exercise programs should be offered which patients are able to easily adhere to. In addition, they also suggest that the prescription of support products should be incorporated as these will contribute to achieving greater immediate functional improvement of individuals.

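### The protocol sets its two post-baseline assessments at day 7 and discharge in one section and at day 15 and 1 month in others, so the time point of the final Barthel comparison is not fixed

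*Protocol article*

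**What the plan says.** All references are to the protocol article.

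- **Evaluations and study plan.** Three assessments: a baseline, then "the second assessment after seven days, and a third final assessment, before the patients are discharged from hospital". The same section repeats this after describing randomisation: "one after seven days, considered as the follow-up assessment, and another at hospital discharge, considered as the final assessment". It sends the reader to Table 1 for detail.
- **Work plan and visit structure.** Three planned evaluation visits: a baseline before randomisation and "two follow-up visits 15 days and 1 month after the first visit". Telephone contacts at 3 and 6 months after randomisation are added.
- **The section headed "Follow-up visits at 15 days and 1 month".** It repeats those times and gives a site away from the ward: "The follow-up visits will be completed in the Clinical Teaching Assistance Unit in the Faculty of Psychology".
- **Interventions.** The exercise programme lasts one month. "After 15 days of the program, the second evaluation will be carried out", and the load may then be adapted. ADL re-education and the evaluation for support products are placed before discharge.
- **Discussion.** The intervention is described as supervised and home-based, "for implementation after their discharge from hospital".
- **Table 1.** Columns are study months. Baseline is marked in months 2-3. The follow-up row and the "FINAL ASSESSMENT" row are both marked only under close-out, months 9-12. The telephone contacts have no row.
- **Data analysis.** The intervention effect is tested by a repeated-measures ANOVA with time and group as factors.

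**The concern.** The Barthel Index is the main variable and the basis of the sample size. A reader cannot tell from the protocol when its final value is measured. Staff who follow one section would collect it on the ward at discharge. Staff who follow another would collect it at a university unit one month after the first visit. These are different endpoints.

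The discharge version has problems of its own:

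- Discharge happens after randomisation, on a date that varies by patient. It may depend on functional recovery, which is close to what the Barthel Index measures, so its timing could differ between arms.
- It is not a common time level, which is what the ANOVA's time factor needs. A patient discharged before day 7 would have the final assessment before the follow-up one.
- It may fall before the one-month exercise programme is complete. On the Discussion's wording it falls before the home-based part begins.

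Sample/participants also makes non-completion of the follow-up and final assessments a withdrawal criterion, so who counts as withdrawn depends on which schedule applies.

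**Working it through.** **1. The schedule statements side by side.**

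| Section | Second assessment | Final assessment | Origin or place |
|---|---|---|---|
| Evaluations and study plan (stated twice) | 7 days | hospital discharge | hospital |
| Work plan and visit structure | 15 days | 1 month | counted from first visit |
| Follow-up visits section | 15 days | 1 month | university unit |
| Interventions | 15 days | not stated | counted from programme start |
| Table 1 | months 9-12 | months 9-12 | study calendar |

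**2. Could they be complementary?** No. Both text versions count three assessments in total, one at baseline and two after it. Day 7 plus discharge and day 15 plus 1 month would make five.

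**3. Does Table 1 decide?** No. It also lists database preparation and dissemination, so it reads as a project calendar rather than time since each patient's randomisation. It shows neither text version.

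**4. Do the origins agree?** Not fully. The Baseline visit section puts randomisation at the end of the first visit, so those two origins nearly coincide. Programme start is separate: the programme is explained at a further visit, and the control group has no programme start. Only the first visit or randomisation can serve as an origin common to both arms.

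**5. The plan's own power figure.** Inputs from the sample-size paragraph: difference 17 points, 25 per arm, two-sided alpha 0.05, power 90%, with a beta risk of 0.2 also stated. No SD is given, so the figure cannot be reproduced, only solved backwards (normal approximation):

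SD = 17 / [√(2/25) × (z for alpha + z for power)]

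- 90% power: 17 / [0.2828 × (1.960 + 1.282)] = 18.5
- 80% power: 17 / [0.2828 × (1.960 + 0.842)] = 21.5

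**6. What early measurement could do (illustration only).** Take SD 18.54, so the standard error of the difference is 18.54 × 0.2828 = 5.24. Assume a share f of the 17 points is present at the final assessment. Power = Φ(17f / 5.24 − 1.96).

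| f (assumed) | Difference | Power |
|---|---|---|
| 1.00 | 17.0 | 90% |
| 0.75 | 12.75 | 68% |
| 0.50 | 8.5 | 37% |
| 0.25 | 4.25 | 12% |

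Neither f nor the SD comes from the documents. The table shows only that the time point matters to the power claim if the effect builds up over the programme.

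**The case against.** The contradiction itself is hard to dispute: each version is written out in full prose and repeated. The fair objections concern what may be built on it, and they stand.

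- **A third schedule.** A reader might take Table 1 as a third, conflicting schedule. It is in calendar months, its intervention rows are blank in the text at hand, and marks may have been lost. It supports only the statement that the table does not show the visits it is cited for.
- **Most of the programme still undelivered at discharge.** A reader might infer this by counting sessions: two a day for about 30 days is 60, of which 14 (23%) fall by day 7. But ADL re-education is placed before discharge and bears directly on the Barthel Index, so exercise sessions are a poor measure of exposure. No length of stay is given. Exercise exposure at discharge could be none on the Discussion's wording, or nearly complete if stays are long and the programme runs in the unit.
- **A specific loss of power.** A reader might assume a length of stay and linear accrual and quote a figure far below 90%. That also requires the 17 points to be a one-month effect, and the article does not say when the cited study measured it.
- **Bias.** A reader might call the discharge contrast biased. A randomised intention-to-treat comparison at discharge estimates a different quantity. A timing difference by arm is possible but not shown.

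**Conclusion.** The point holds as an internal contradiction about when the main outcome is measured, and it must be resolved. Evaluations and study plan conflicts with Work plan and visit structure and with the follow-up visits section on both assessments, and with Interventions on the second. The time levels of the ANOVA and the time point of the final Barthel comparison are therefore not fixed. This rests on the text alone and needs no assumption.

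The consequence of following the discharge version is conditional. If the effect builds up over the month and discharge comes before the programme ends, the contrast would be smaller than the 17 points behind the stated 90% power. The documents do not allow that loss to be quantified.

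**What to change.** 1. Use one outcome-assessment schedule, counted from the same origin in both arms (first visit or randomisation), with assessments at day 15 and 1 month as two sections already plan. Name the Barthel Index at 1 month as the primary time point.
2. Delete the day-7 and discharge wording under Evaluations and study plan, or keep a discharge measurement as descriptive only.
3. Make Table 1 show, per patient, the baseline, day-15 and 1-month visits and the 3- and 6-month telephone contacts.
4. The sponsor must reconcile the statements on where and when the programme runs (Evaluations and study plan, Interventions, Discussion). This review takes no position on which is right.

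The cost is protocol wording and a corrected table. No visits are added, because the day-15 and 1-month visits are already planned.
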